#### 7.4. Secondary endpoints

Statistical analyses for all secondary outcome variables listed in chapter 6.3 including quality of life and the additional outcomes at the follow-up assessment (T4, Visit 12) will be analogous to the primary outcome analyses. We will use the same regression model as described in chapter 7.3 but will replace the dependent variable in the SPSS syntax code (see Appendix 4) with all secondary outcomes, successively and include the baseline value of the secondary outcome as a covariate. Hence, we calculate for each secondary outcome variable a separate regression model. Presentation of model results will be identical to primary outcome analyses (see Appendix 5).

Note, however, that all analyses of functional brain related outcome measures and all outcomes from sub-studies are the responsibility of the respective investigators. The statisticians of the IMIS will not perform any statistical analyses located in this field.

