## 11.1 Sample size calculation

The sample size for **Study A** and **Study B** is calculated separately for each study using a two-sided t-test (significance level  $\alpha=0.05$ ) with a power  $1-\beta=80\%$  based on a medium expected effect size of  $d=0.6$ . Previous studies in ADHD have shown similar or larger effect sizes for tDCS. This result leads

to a required sample size of 45 patients per group (G\*Power3.1); assuming 10% drop-out, the total sample size consists of 200 randomized patients (100 patients for each study). In **Study A**, 50 patients will be allocated randomly to Arm A, whereas the remaining 50 patients will be randomized to Arm B. The same procedure will be repeated for **Study B**.

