#### *Secondary Outcomes*

Secondary outcomes relating to further clinical measures as well as quality of life and the additional outcomes at the follow-up assessment (T4, Visit 12) will be analyzed in a similar way. Analysis of functional brain related outcome measures and all outcomes from substudies are the responsibility of the investigators named in 2.3.

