### **7.6. Missing values**

In the primary analysis of the primary endpoint, we will use multiple imputations to account for missing data. Multiple imputations are currently the preferred method for dealing with missing values (Graham et al., 2003) under the assumption of missing at random (MAR).

Sensitivity analyses will be performed to investigate the potential impact of missing data, in particular, by using data of both the end-of-treatment (V11) and follow-up (V12) assessments in a mixed-effects model repeated measures analysis to estimate the treatment contrast at V11, a complete case analysis and specification of a range of plausible values for missing data (worst-best case scenarios under a missing-not-at-random (MNAR) assumption) to evaluate the potential departure of statistical estimates and inference from those obtained in the primary analysis under an MAR assumption.

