| - concurrent pharmacological treatment of ADHD                                                                                                                | exclusion_11  |

*Note:* Variables listed in the second column of this table will be dichotomous (1=fulfilled, 0=not fulfilled).

### 10.3 Appendix 3

```
DESCRIPTIVES VARIABLES= nback_oa  
/STATISTICS=MEAN STDDEV MIN MAX.
```

```
FREQUENCIES VARIABLES= nback_oa  
/NTILES=4  
/STATISTICS=STDDEV VARIANCE RANGE MINIMUM MAXIMUM MEAN MEDIAN  
/ORDER=ANALYSIS.
```

```
EXAMINE VARIABLES= nback_oa  
/PLOT NONE  
/PERCENTILES(5,10,25,50,75,90,95) HAVERAGE  
/STATISTICS DESCRIPTIVES EXTREME  
/CINTERVAL 95  
/MISSING LISTWISE  
/NOTOTAL.
```

```
EXAMINE VARIABLES= nback_oa  
/PLOT=BOXPLOT  
/STATISTICS=NONE  
/NOTOTAL  
/ID=vp_nr.
```

*Note:* This is an example for outlier detection conducted in the statistical software SPSS for Windows. The SPSS syntax code checks the primary outcome in **Study A**, the overall accuracy in the n-back working memory task (variable *nback\_oa*), with descriptive statistics and boxplots for plausibility reasons.

## 10.4 Appendix 4

```
REGRESSION
/DESCRIPTIVES MEAN STDDEV CORR SIG N
/MISSING LISTWISE
/STATISTICS COEFF OUTS CI(95) R ANOVA
/CRITERIA=PIN(.05) POUT(.10)
/NOORIGIN
/DEPENDENT nback_oa_T3
/METHOD=ENTER
stimulation
center
sex
*puberty status
age
IQ
nback_oa_T2
.
```

Note: This is an example for the primary outcome analyses in the statistical software SPSS for Windows. The SPSS syntax code shows a regression analysis with the primary outcome in **Study A** (overall accuracy in the n-back working memory task, variable *nback\_oa\_T3*) as dependent variable. The variables *stimulation* (coded as 1=anodal tDCS stimulation and 0=sham stimulation), *center*, *sex*, *puberty status* (only to be included if correlation with age is not too large), *age*, *IQ*, and the baseline value of accuracy in the respective tasks at T2 (Visit 0, *nback\_oa\_T2*) enter the regression model as independent variables.

## 10.5 Appendix 5

Table 3 below illustrates how empirical results of primary outcome analyses will be summarized. Here, some fake results of **Study A** are presented. Model results of **Study B** will be presented in a similar way.

Table 3

*Model results for Study A*

| Model          | IV               | b | S.E. | CI [ b ] | $\beta$ | p |
|----------------|------------------|----------|------|-----------------|---------|----------|

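### The SAP names no missing-data method for secondary and V12 outcomes; read literally, V12 estimates are complete-case and leave V11 values unused (minor)

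*Combined protocol and SAP*

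**What the plan says.** SAP 7.6, the section on missing values, opens: "In the primary analysis of the primary endpoint, we will use multiple imputations to account for missing data". Protocol 11.3.3 limits imputation in the same way. SAP 7.6 then lists sensitivity analyses: a mixed model of V11 and V12, whose stated target is the V11 contrast; a complete-case analysis; and worst-best scenarios judged against the primary analysis.

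For secondary and V12 outcomes, protocol 11.3.3 says only that they "will be analyzed in a similar way". SAP 7.4 calls them analogous to the primary analysis and gives one concrete instruction: the analysts "will replace the dependent variable in the SPSS syntax code (see Appendix 4) with all secondary outcomes, successively", with that outcome's own baseline value as covariate and a separate model for each outcome. The Appendix 4 code is a linear regression carrying the option "MISSING LISTWISE". It shows no imputation or pooling step.

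SAP 5.2 lists a missing V12 among the violations relevant to the V12 analysis. It does not say whether that list governs the per-protocol set only or the intention-to-treat set too.

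**The concern.** No section states a missing-data method for secondary or V12 outcomes. The one section on missing data confines imputation to the primary endpoint, and the one operational instruction for secondary outcomes points to code that drops incomplete records. Two competent statisticians could therefore produce different V12 results from the same SAP.

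This matters most at V12. SAP section 2 includes improvement after 4 weeks in the trial's aim, and SAP 7.3 puts the emphasis on effect estimates and their intervals, so a shift in the estimate counts even where no formal claim is made. For a child who attends V11 and misses V12, the V11 score is likely to be the best predictor of the missing value, but the literal model adjusts only for baseline. If tDCS children who did poorly at V11 return less often, and sham children do not behave likewise, the lasting effect is overstated. The data needed to correct this are already collected.

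**Working it through.** **1. The plan's own figure.** Protocol 11.1 gives a two-sided t-test, alpha 0.05, power 80%, d = 0.6, and a "required sample size of 45 patients per group". Exact noncentral-t power is 80.4% at 45 per group, and 45 is the smallest such n. Inflating for loss, 45 / (1 - 0.10) = 50 per arm, or 100 per study. The figure reproduces.

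**2. Loss of numbers.** At 10% loss a listwise model keeps about 100 x 0.90 = 90 children per study. Unadjusted power at d = 0.6 falls from 84.4% (50 per arm) to 80.4% (45 per arm). That cost is already in the sample size. The documents give no separate loss rate for V12; at an assumed 20% (40 per arm) power would be 75.5%. The calculation was not made for any secondary outcome, so these figures only indicate scale.

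**3. Bias at V12.** Assumptions, none of them from the documents: true effect 0.60 SD at V11 and V12; correlation of baseline with each, 0.6; V11-V12 correlation 0.7. The loss rate of about 10% is the plan's. The analysis is ANCOVA on treatment and baseline, listwise.

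Results from 4,000 simulated trials of 50 per arm:

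| V12 loss | Full data | Listwise | Imputation using V11 |
|---|---|---|---|
| Random | 0.599 | 0.600 | 0.600 |
| Depends on baseline | 0.602 | 0.603 | 0.603 |
| Depends on V11 in tDCS arm only (logit slope 1.2 per SD), random in sham | 0.604 | 0.642 | 0.604 |

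A large-sample simulation (400,000 children per setting) with the third mechanism gave 0.634 and 0.638 at 10% loss for slopes 1.0 and 1.5, and 0.657 and 0.683 at an assumed 20%. Imputation using V11 returned 0.595-0.603.

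If loss follows V11 equally in both arms, measured from each arm's own mean, the arms shift together and the bias cancels. If both arms follow one rule on the raw score, a real V11 effect makes loss heavier in the sham arm, and the listwise estimate moves slightly the other way, towards no effect.

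**4. Hand check.** With slope s and loss rate q, the mean V11 score among tDCS completers rises by at most about s x q. The covariance of V11 and V12 given baseline is 0.7 - 0.6 x 0.6 = 0.34. First-order bias is then about s x q x 0.34. For s = 1.0 this is 1.0 x 0.10 x 0.34 = 0.034; for s = 1.2 it is 0.041. This approximation runs slightly high, and it agrees with the simulated excess of about 0.03-0.04.

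**5. Relative size.** With 45 per arm and baseline correlation 0.6, SE = sqrt((1 - 0.36) x 2/45) = 0.169. A bias of 0.642 - 0.604 = 0.038 is 0.038 / 0.169 = 0.22 SE.

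**The case against.** Appendix 4 is labelled an example and is written for the primary outcome, which SAP 7.6 says is imputed. Run on imputed data, the listwise option removes nobody for an imputed variable, so that line alone cannot prove that secondary outcomes are complete-case. SAP 7.4's description of the secondary analyses as analogous leaves room for imputation, and the protocol synopsis mentions imputation in the primary analysis without naming the endpoint. This stands: the documents are ambiguous and do not order deletion.

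A reader might infer that drop-outs leave every secondary analysis, in contradiction of a promise to analyse all randomised children. The documents do not support that. Each outcome has its own model, so a child missing only V12 stays in the V11 models. Children who stop treatment are still asked to attend V11 and V12 (protocol 11.3.2). The explicit all-randomised sentences in SAP 5.2 and protocol 11.3.2 concern the primary analysis; SAP section 5 says more generally that results use the intention-to-treat and per-protocol sets.

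The bias also needs V11-dependent loss that differs by arm. In a double-blind trial whose sham is described as indistinguishable, the documents give no particular reason to expect it. No harm was shown for V11 secondary outcomes. Finally, V11 data cannot directly rescue quality of life: KIDSCREEN-27 is scheduled only at screening and V12, although SAP 6.3 also lists it at V11.

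The omission itself survives. The planned mixed model yields no V12 estimate as specified, and no other text fills the gap.

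**Conclusion.** The point holds as a minor one. The SAP does not specify how missing secondary and V12 outcomes are handled, and its most literal reading is a complete-case analysis that ignores V11 values when V12 is missing. The children lost are only those missing a variable in a given model.

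Under the assumed correlations, an effect of 0.60 SD would be estimated at about 0.63-0.64 at 10% loss if V12 loss depends on V11 in the tDCS arm only, an excess of roughly 0.2 standard errors. There is none if loss is random, depends on baseline, or follows V11 equally in both arms. The loss of precision at 10% is already budgeted. The reason to act is that the choice should be fixed before the data are seen, and a method less prone to bias is available from data already collected.

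**What to change.** - **V12 outcomes also measured at V11 (task measures, ADHD rating).** In SAP 7.4 and 7.6, either report the V12 treatment contrast from the mixed model of V11 and V12 already planned, with the arm effect allowed to differ by visit, or extend the multiple imputation to these outcomes. The imputation model should hold arm, the V0 or screening, V11 and V12 values, and the model covariates. The mixed model is the simpler route and gives the V11 contrast as well.
- **KIDSCREEN-27.** Impute using other V11 variables, such as the ADHD rating, or label the analysis complete-case.
- **Appendix 4.** Show the imputation and pooling step, so that the example matches SAP 7.6.
- **Listwise model.** Keep it as a sensitivity analysis and report the number analysed per arm.
- **SAP 5.2.** State which analysis set the V12 violation list governs.

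No new data are needed. The cost is extra programming and a model specification for each outcome. With about 50 children per arm and several covariates, the imputation models would have to be kept small.

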#### 7.5. Safety analyses

For safety evaluations, we will use descriptive statistics for each study (**Study A** and **Study B**) separately and combined. We will tabulate absolute and relative frequencies of adverse events (AEs) and severe adverse events (SAEs) by study arm (tDCS and sham), severity and investigator-assessed relation to investigational treatment. No statistical tests will be performed for (S)AEs which are expected to be rare. In addition, safety and tolerability of tDCS stimulation will be evaluated with the standardized safety questionnaire and differences between study arms (tDCS and sham) will be analyzed in an analogous way to endpoint analysis. We will visualize empirical findings with bar charts and box plots.

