## 1.2 Risk-benefit ratio

### 1.2.1 Risk-benefit ratio concerning the medical device

In the design and performance stage of Starstim's NEC box, general requirements for basic safety and essential performance were created according to Independent Ethics Committee (IEC) 60601-1:2005, IEC 60601-1-2:2007 and IEC 60601-1-11:2010. Afterwards, the device was verified and validated both in-house and in a third-party laboratory to confirm its compliance to the aforementioned standards. Thereafter, the risk analysis in compliance with ISO 14971:2007 and literature review were performed to assure the device is safe. The most common adverse effects reported in the literature are sensations under the electrodes (tingling, burning, itching), fatigue and redness or skin irritation under the electrode (Brunoni et al., 2011).

Based on most recent clinical evidence (Bikson et al., 2016), the use of conventional tDCS protocols in human trials ( $\leq 40$  min,  $\leq 4$  milliamperes,  $\leq 7.2$  Coulombs) has not produced any reports of serious adverse effect or irreversible injury with over 33.200 sessions and 1.000 subjects with repeated sessions. This includes a wide variety of subjects, including persons from potentially vulnerable populations. Adverse effects of active vs. sham tDCS include itching (39.3% vs. 32.9%,  $p>0.05$ ), tingling (22.2% vs. 18.3%,  $p>0.05$ ), headache (14.8% vs. 16.2%,  $p>0.05$ ), burning sensation (8.7% vs. 10%,  $p>0.05$ ) and discomfort (10.4 % vs. 13.4 %,  $p>0.05$ ). Post-market surveillance activities performed by Neuroelectronics in the European clinical market including the Clinical Evaluation Report confirm that no SAEs have been reported to date. All adverse events (AE) reported are rare, minor and transient.

The device Starstim32 used in the current proposal allows the use of an optimized multi-channel montage which provides a more targeted stimulation of the critical brain area.

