### 2.1 Study objectives

#### 2.1.1 Primary objectives

- Investigate effect sizes of changes in neuropsychological performance and study safety and tolerability of multi-channel anodal tDCS targeting the left dorsolateral prefrontal cortex (dlPFC) (**Study A**) or the right inferior frontal gyrus (rIFG) (**Study B**) in children and adolescents with ADHD

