### 2.2 Endpoints

#### 2.2.1 Primary endpoints

- **Study A:** Overall accuracy in an *n-back* task (assessing working memory): changes from V0 to V11
- **Study B:** Overall accuracy in a *Flanker* task (assessing inhibitory/interference control): changes from V0 to V11
- **Study A/B:** Ratings and observations of safety and tolerability aspects at all visits (1-10)

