## **8.4 Effects**

### **8.4.1 Adverse effects of medical devices**

An adverse effect is any untoward and unintentional reaction to the IMD application. An adverse event will be categorised as an adverse effect if a causal relationship between the event and the IMD application is at least deemed possible or cannot be excluded all together. The most common AE associated with the employed device or rather tDCS in general are sensations under the electrodes (tingling, burning, itching), fatigue and redness or skin irritation under the electrode.

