### 2.1 Primary objective

The primary objective of the E-StimADHD study is to investigate effect sizes of changes in neuropsychological performance, study safety and tolerability of multi-channel anodal tDCS (anodal tDCS vs. sham stimulation) targeting the specific brain region left dlPFC (**Study A**) or rIFG (**Study B**) in children and adolescents with ADHD.

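### Adverse events are primary safety endpoints, but SAP 7.5 plans only counts and percentages by arm, so the analysis will not say how large a harm the data exclude

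*Combined protocol and SAP*

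**What the plan says.** The SAP (2.1) sets out to "investigate effect sizes of changes in neuropsychological performance, study safety and tolerability of multi-channel anodal tDCS", and the protocol (2.1.1) likewise names "safety and tolerability of multi-channel anodal tDCS" among its primary objectives. Protocol 2.2.1 lists a matching primary endpoint for both studies: "Ratings and observations of safety and tolerability aspects at all visits (1-10"). SAP 6.2 breaks this into the safety questionnaire, EEG abnormalities, and the number, type and severity of AEs and SAEs, all defined as primary.

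For the analysis, SAP 7.5 says "we will use descriptive statistics for each study", separately and combined. AEs and SAEs are tabulated by arm, severity and assessed relation to treatment. It then adds: "No statistical tests will be performed for (S)AEs which are expected to be rare". For the questionnaire, "differences between study arms (tDCS and sham) will be analyzed in an analogous way to endpoint analysis". The endpoint analysis in SAP 7.3 is a covariate-adjusted regression that stresses effect estimates with 95% intervals. Its one decision rule is to conclude superiority of tDCS when the coefficient is positive with p below 0.05.

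On how common AEs are, protocol 8.4.1 states: "The most common AE associated with the employed device or rather tDCS in general are sensations under the electrodes (tingling, burning, itching"), among others. Protocol 1.2.1 reports literature rates, beginning "Adverse effects of active vs. sham tDCS include itching (39.3% vs. 32.9" per cent), with tingling at 22.2% against 18.3%. The same section describes the AEs seen in the manufacturer's post-market surveillance as rare.

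**The concern.** A primary endpoint is summarised with less than the secondary endpoints receive. Every secondary outcome handled by the trial statisticians gets a regression estimate with a confidence interval (SAP 7.4); AEs and SAEs get percentages only.

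The reason offered covers AEs and SAEs alike. It suits SAEs. It does not suit AEs if electrode sensations are recorded as AEs, as 8.4.1 implies. Where events really are rare, the upper confidence limit is the informative figure, and none is planned.

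The participants are aged 10 to 18, and SAP 6.2 intends these data to feed a global safety assessment of tDCS in children and adolescents. Similar percentages in the two arms, or no SAEs, would leave open how large an excess of harm remains possible. Neither document says how a safety conclusion will be drawn.

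**Working it through.** **Plan's own figure.** Protocol 11.1: two-sided t-test, alpha 0.05, power 80%, d = 0.6. With the noncentral t distribution, 44 per group gives 79.5% power and 45 gives 80.4%, so 45 is reproduced. Allowing for 10% drop-out, 45 / 0.90 = 50 per arm, or 100 per study.

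**Which n applies to safety.** The SAP 5.1 safety set is everyone randomised who started at least one session. Children who drop out after the first session stay in it, so 50 per arm per study is the planning number, and 100 per arm for A and B combined.

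**Zero events.** Exact (Clopper-Pearson) two-sided 95% upper limit for 0 out of n: 1 − 0.025^(1/n).
- n = 50: 1 − 0.025^(1/50) = 7.1%
- n = 100: 1 − 0.025^(1/100) = 3.6%

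**Common AEs.** 95% half-width of a risk difference: 1.96 × √[p1(1 − p1)/n + p2(1 − p2)/n]. The rates come from protocol 1.2.1. That section does not state their denominator, so I assume they are proportions of children.
- Itching, n = 50: 1.96 × √[(0.2386 + 0.2208)/50] = 18.8 points. The difference is 39.3 − 32.9 = 6.4 points, so the interval runs from −12.4 to +25.2.
- Itching, n = 100: half-width 13.3 points, interval −6.9 to +19.7.
- Tingling, difference 3.9 points: half-width 15.7 points at n = 50 (upper limit 19.6) and 11.1 at n = 100 (upper limit 15.0).

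**Would a test help?** At the quoted itching rates a two-proportion test has about 10% power at 50 per arm and 15% at 100. The SAP's decision not to test AEs is therefore reasonable; the gap is the missing interval.

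**Questionnaire.** If the analysis really follows SAP 7.3, it yields a 95% interval. Without covariate gain the half-width is t(0.975) × √(2/n): 0.40 SD at n = 50 and 0.28 SD at n = 100. So an upper limit will exist. What is missing is a statement of how it is to be used, because the SAP 7.3 rule concerns benefit and has no counterpart for harm. The examination plan schedules the questionnaire only at V1 to V10, so there is no baseline value to adjust for, and the SAP does not say how ten sessions are reduced to one score. These widths therefore describe a generic single score.

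**The case against.** The strongest reply is that the commonest effects are not left without inference. Itching and burning are rated on the safety questionnaire (protocol 7.3), which does get a between-arm analysis, and participants are asked about AEs separately (8.2). The 1.2.1 rates come from the literature, the same section calls post-market AEs rare, and 1.2.2 reports a low AE rate in the consortium's own studies. The SAP sentence could also mean only those AEs that turn out to be rare. Descriptive AE reporting is usual in a phase IIa trial, a DSMB reviews AEs, SAEs and the questionnaire (8.9), and exact limits could be computed later from the tables.

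Much of this stands, and it keeps the point modest. It does not close the gap. Protocol 8.4.1 does label the sensations AEs, and on the narrower reading nothing is specified for AEs that are frequent. The DSMB protects participants during the trial but supplies no interval for the final analysis. Limits can be recovered from the tables only if these count children: protocol 8.3.1.1 has a repeat episode after recovery entered as a new record, and SAP 7.5 does not say whether events or children are tabulated. The wider pooled analysis mentioned in SAP 6.2 may include intervals, but its details are left to another document.

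A reader might infer more than the documents support:
- That the whole safety objective lacks an upper bound. This is not so for the questionnaire, as shown above.
- That a non-significant questionnaire contrast will be taken as proof of safety. Neither document says so; they simply give no rule.
- That a 0.5-SD harm on the questionnaire would be missed 30% of the time. That holds for one study at 50 per arm with no covariate gain. With A and B combined, as SAP 6.2 and 7.5 plan, it is about 6%. The 0.5 SD is itself an assumption found in neither document.

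**Conclusion.** The point holds as a gap in planned reporting. AE and SAE endpoints defined as primary have no prespecified risk difference, interval or upper limit, and the stated reason conflicts with the protocol's own description of common AEs. In size, the plan leaves unstated that no SAEs in 50 children excludes only rates above 7.1% (3.6% for 100), and that a difference like the quoted one for itching would carry an uncertainty of about ±19 points per study or ±13 combined.

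These figures assume full recruitment, 50 per arm in the safety set, and literature rates that apply per child. They illustrate precision; they do not show that tDCS is harmful or that SAEs are common. Neither document sets an acceptable margin of harm, and I do not supply one. The change is worth making because it is cheap and lets the primary safety objective be answered in terms of what the data exclude.

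**What to change.** Amend SAP 7.5 as follows:
- Remove rarity as the reason for the AE analysis; it may stay for SAEs.
- For AEs overall, device-related AEs, and each AE type above a fixed frequency (for example 5% in either arm), report the proportion of children affected per arm and the tDCS minus sham risk difference with a 95% confidence interval, per study and for A and B combined with stratification by study.
- For SAEs and any row with zero events, give the exact (Clopper-Pearson) 95% upper limit per arm.
- Word the safety conclusion from these limits and from the interval of the questionnaire contrast, and state that non-significance or equal counts is not evidence of safety.

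This needs no AE hypothesis test, no new data and no additional participants. The cost is some SAP wording, a few more table columns, and a more cautious safety statement.
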